### Attrition and adherence

Participants will be withdrawn from the study if there is a change in medications or if they are unable to attend follow ups. Adherence to aerobic exercise and stretching protocols will be tracked using online daily diaries (using Research Electronic Data Capture [REDCap]) sent out via email. REDCap is a secure, web-based application for data capture. Diaries will be completed by all participants for the duration of the study and submitted on their mobile device. Daily diaries will track symptomatology before and after prescribed exercise, physical activity beyond what is prescribed, daily symptom burden rating on a VAS and medication usage. In the event that the activity diary is not being completed, reminders will be sent out by the study team. A record will be kept of sent reminders.

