### Study group

Subjects will be eligible to participate based on the following inclusion criteria: 1) aged 18–65 years; 2) diagnosis of mTBI based on American Congress of Rehabilitation Medicine criteria [28] 3) diagnosis of PPCS based on ICD-10 postconcussional syndrome criteria [29] for a minimum of 3 months to a maximum of 5 years; 3) exercise intolerance, described as acute exacerbation of post-concussive symptoms with exercise; 4) maintenance of a stable pharmacological regiment for a minimum of one month prior to intervention start with the requirement of maintaining this regiment for the duration of the trial. Exclusion criteria includes past medical history of other neurological condition or psychiatric condition (other than depression and/or anxiety), a prior moderate or severe traumatic brain injury, or a history of cardiopulmonary or chronic musculoskeletal condition.

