### Sample size

A power calculation using significant outcomes for RPQ in a neurorehabilitation/exercise intervention suggested 46 participants should be included to find significant improvement, with an alpha of 0.05 and 80% power [59]. With an anticipated dropout rate of 1–5 participants per group we will recruit 56 participants for this trial.

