### Analysis

The primary clinical outcome is the RPQ at 6-weeks of intervention. For the clinical outcome measures, two separate analyses will be run:
Outcome measures will be analyzed using two-way mixed ANOVA at baseline and 6-week timepoints. Two-way mixed ANOVA allows for analysis of group by time interaction effect. If a statistically significant group by time interaction effect is detected, indicating that group effect varies with time, or time effect varies with the group, simple effect testing will be used to analyze group effect broken down by time or time effect broken down by group. Should there be missing values, generalized estimating equation analysis will be employed.Outcome measures between groups (delayed-start vs. immediate start) following the aerobic exercise intervention only will be analyzed using two-way mixed ANOVA at the three primary timepoints: baseline, 6-weeks and 12-weeks.

The HERMES MRS data will be analysed to quantify GABA and glutathione levels using Gannet3, a spectral analysis tool. The PRESS MRS data will be analyzed to quantify NAA, glutamate, creatine and choline. Metabolite levels will be compared using an ANOVA model comparing groups at each of the three timepoints (as above). Additional exploratory analyses will investigate the correlations between metabolite levels and symptom burden. Whole brain ASL data will be processed to provide quantitative maps of tissue perfusion (cerebral blood flow) and group data will be compared on a whole brain basis. If no differences are detected, regional analyses may be applied. Resting state fMRI data will investigate differences in functional connectivity between groups and time points using both independent component analysis and seed-based approaches.

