## Discussion

This study will expand our understanding of the utility of sub-symptom threshold aerobic exercise as an intervention for the treatment of PPCS as it has not previously been investigated in an adult population. The use of MRS for analysis of brain metabolites in addition to blood biomarker investigations will provide greater understanding of the pathophysiology of this patient cohort and their response to intervention. This trial will expand on previous work in the domain of adolescent SRC to evaluate this intervention in an adult PPCS population with diverse etiology of injury and chronic symptomatology. Should this trial be successful, it will be largely generalizable to the adult PPCS population. The proposed intervention is easy to implement, low cost and a novel non-pharmacological treatment option for a patient population with high rates of polypharmacy. An aerobic exercise intervention such as the one described has the potential to not only improve exercise intolerance, but also treat multiple chronic symptoms experienced by adults whose quality of life and activity has been greatly limited by PPCS.

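### Withdrawing randomised participants from the study after a medication change can bias the 6-week RPQ comparison in either direction

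*Protocol article*

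**What the plan says.** All references are to the protocol article.

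- Attrition and adherence, where the rule reads: "Participants will be withdrawn from the study if there is a change in medications or if they are unable to attend follow ups".
- Study group: the inclusion criteria ask for a stable drug regimen for at least a month beforehand, "with the requirement of maintaining this regiment for the duration of the trial".
- Analysis: "The primary clinical outcome is the RPQ at 6-weeks of intervention". The method is given as "Outcome measures will be analyzed using two-way mixed ANOVA at baseline and 6-week timepoints", with the fallback "Should there be missing values, generalized estimating equation analysis will be employed".
- Sample size: "With an anticipated dropout rate of 1–5 participants per group we will recruit 56 participants for this trial".
- Blinding and randomization: only the data analyst is blinded.

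The article nowhere says that a withdrawn participant still gives a 6-week RPQ, or that all randomised participants are analysed as allocated.

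**The concern.** The rule acts on an event that happens after randomisation and is plausibly tied to the outcome. Worsening headache, mood or sleep may lead to more medication, and improvement may lead to less. Either is a change. Participants and study staff know the allocation, so the frequency of changes and the reasons for them can differ between arms.

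If the rule is followed as written, the participants it removes before week 6 supply no primary outcome. The 6-week comparison then rests on those whose medication stayed the same, a group no longer protected by randomisation. A later analysis plan can choose the analysis set, but it cannot analyse outcomes that were not collected.

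The attendance part of the rule is weaker, because inability to attend is partly ordinary loss to follow-up. It still matters here, since the RPQ is a questionnaire and need not depend on a visit.

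**Working it through.** **Inputs from the article.** 46 participants needed, 56 recruited, 1–5 losses per group (Sample size); 28 per arm (Treatment arms); MCID 4.6 RPQ points (Primary outcome measure); "with an alpha of 0.05 and 80% power" (Sample size).

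**Assumptions, not in the article.** SD of the RPQ 8–12 points. Withdrawn participants are worse than stayers by g = 0.5–1.0 SD.

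**1. The plan's own figure.** 46 + 2 × 5 = 56, so the recruited number reproduces at the upper end of the allowance, which is 10/56 = 17.9% lost. The 46 cannot be checked, because no effect size or SD is given. The allowance protects the number of participants, not their comparability.

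**2. Size of the bias.** Let k be the number withdrawn in an arm of 28. The stayers' mean differs from the full arm's mean by (k/28) × g × SD, so

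bias in (AEP − SP) = (k_SP − k_AEP)/28 × g × SD.

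A higher RPQ is worse, so a positive value counts against AEP. With 5 withdrawn from SP and 1 from AEP, the first factor is 4/28 = 0.143:

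| SD | g = 0.5 | g = 1.0 |
|---|---|---|
| 8 | 0.57 (12% of 4.6) | 1.14 (25%) |
| 10 | 0.71 (16%) | 1.43 (31%) |
| 12 | 0.86 (19%) | 1.71 (37%) |

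The reverse split gives the same values with a negative sign, in favour of AEP. Equal numbers with equal g give zero.

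**3. Check by simulation.** SD 10, baseline correlation 0.5, withdrawal linked to the 6-week score. A 5 v 1 split gave a bias of ±1.4 points on the 6-week score and ±0.7 on change from baseline. With two time points, the group-by-time interaction is a comparison of changes, so in this scenario 0.7 points (0.7/4.6 = 15%) is closer to what the planned test would see. With 3 v 3 and 5 v 5 the bias was within 0.02.

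**4. Direction.** Take mean changes of −3 (SP) and −7.6 (AEP), SD 10, true difference −4.6.
- If half of those worsening by more than 5 points and 30% of those improving by more than 15 change drugs in both arms, the stayers' difference is about −3.6 (attenuated).
- If only those worsening by more than 5 points change, 20% of them in SP and 80% in AEP, it is about −5.6 (inflated).

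All these withdrawal probabilities are assumptions.

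**5. The fallback.** Mixed ANOVA on baseline and 6 weeks needs both values. Ordinary unweighted GEE assumes data missing completely at random, and someone withdrawn before week 6 contributes only a baseline value. Neither method corrects loss that depends on an unobserved 6-week score.

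**6. Precision.** 23 per arm at two-sided 0.05 and 80% power implies d = √(2/23) × (1.960 + 0.842) = 0.83. With all 28 per arm, power at that d is Φ(0.826 × √14 − 1.960) = Φ(1.13) = 87%.

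**The case against.** The strongest reply has four parts.

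- **The rule has a purpose.** The stable-regimen criterion shows that it guards against drug changes confounding the exercise effect, and the criterion should reduce the number of changes. That stands, but it does not require outcome collection to stop. A change can be recorded and examined in a sensitivity analysis.
- **The article is condensed.** It does not state outright that the 6-week RPQ goes uncollected, and the full protocol may provide for it. That is fair as to certainty. Still, withdrawal from the study is an explicit rule, no other section softens it, and its natural consequence is loss of later outcomes.
- **A missing-data method is named.** It is, but it does not address this mechanism.
- **Attendance.** The text concerns inability to attend follow-ups. A reader might infer that one missed visit triggers withdrawal, but the wording does not say so. The electronic follow-ups described under Measures come after AEP completion and do not name the RPQ. They show only that remote questionnaires are feasible.

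A reader might also take the Discussion's phrase "a novel non-pharmacological treatment option for a patient population with high rates of polypharmacy" to mean that many participants will change drugs. It describes how many drugs are used, not how often they change over six weeks. The documents give no rate of change.

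**Conclusion.** The point holds as a risk: the rule can bias the primary comparison, with direction and size unknown. Within the protocol's own 1–5 losses per group, the most uneven split gives about 0.6–1.7 RPQ points (12–37% of the MCID) under the assumed SD of 8–12 and g of 0.5–1.0. It gives about half as much on change from baseline in the simulated case, and about zero if number and mechanism match across arms.

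Two stronger readings are tempting but unsupported. One is that the rule necessarily shrinks the treatment effect; AEP participants who worsen may also be withdrawn, and that would inflate it. The other is a shift of 1.9–3.5 points (42–76% of the MCID at SD 10). That requires one arm to lose exactly its worst 10–20% and the other nobody, and 20% of 28 is 5.6, above the planned maximum of 5.

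This should be fixed, and the improvement is cheap. Recruitment was under way when the article was submitted, so an amendment protects outcomes still to be collected.

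**What to change.** Amend the sentence in the attrition and adherence section, and reconcile it with the stable-regimen requirement under Study group, so that neither a medication change nor inability to attend ends outcome collection. In substance:

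- Collect the RPQ at 6 and 12 weeks from every randomised participant who has not withdrawn consent, through REDCap if the visit cannot take place.
- Make the primary analysis include all randomised participants as allocated, whether or not medication changed.
- Record medication change from the daily diaries, which already capture medication use, and treat it as an intercurrent event.
- Add a sensitivity analysis that excludes data after a change.

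Whether medication or the exercise programme changes or continues remains with the investigators.

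Cost: amended wording and an electronic questionnaire link at two dates, with no extra visits. Downside: the main estimate will include some outcomes affected by medication changes, which the sensitivity analysis helps to gauge. The recruited number of 56 does not change.

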### Data management

Participants will be assigned a study ID number at the time of randomization by which they will be identified within the research team. Study data will be entered into a highly secure electronic REDCap database which requires double password protection to enter. Only research team members will have access to this database. Participant information or other data transmitted through USB will be encrypted. USB transfer of information will only be used when absolutely necessary and will be password protected. Paper copies of any data or participant information will be kept in a locked cabinet in a locked room in a locked university building.

All identifying information will be removed once all study participant numbers have been assigned and all data is collected. When data is downloaded for analysis, manuscript writing or abstract preparation all identifying information will be excluded. This information will be downloaded to a password protected SPSS file for analysis. No identifiable information will be retained once data collection is complete. All data will be retained for five years following project completion in accordance with Health Canada retention guidelines.

### Sample size

A power calculation using significant outcomes for RPQ in a neurorehabilitation/exercise intervention suggested 46 participants should be included to find significant improvement, with an alpha of 0.05 and 80% power [59]. With an anticipated dropout rate of 1–5 participants per group we will recruit 56 participants for this trial.

### Analysis

The primary clinical outcome is the RPQ at 6-weeks of intervention. For the clinical outcome measures, two separate analyses will be run:
Outcome measures will be analyzed using two-way mixed ANOVA at baseline and 6-week timepoints. Two-way mixed ANOVA allows for analysis of group by time interaction effect. If a statistically significant group by time interaction effect is detected, indicating that group effect varies with time, or time effect varies with the group, simple effect testing will be used to analyze group effect broken down by time or time effect broken down by group. Should there be missing values, generalized estimating equation analysis will be employed.Outcome measures between groups (delayed-start vs. immediate start) following the aerobic exercise intervention only will be analyzed using two-way mixed ANOVA at the three primary timepoints: baseline, 6-weeks and 12-weeks.

The HERMES MRS data will be analysed to quantify GABA and glutathione levels using Gannet3, a spectral analysis tool. The PRESS MRS data will be analyzed to quantify NAA, glutamate, creatine and choline. Metabolite levels will be compared using an ANOVA model comparing groups at each of the three timepoints (as above). Additional exploratory analyses will investigate the correlations between metabolite levels and symptom burden. Whole brain ASL data will be processed to provide quantitative maps of tissue perfusion (cerebral blood flow) and group data will be compared on a whole brain basis. If no differences are detected, regional analyses may be applied. Resting state fMRI data will investigate differences in functional connectivity between groups and time points using both independent component analysis and seed-based approaches.

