### Interventions

#### Treatment arms

Once screening is complete and a participant is enrolled, they will be randomized to either begin the aerobic exercise protocol immediately (AEP, *n* = 28), or begin the aerobic exercise following a precursor placebo-like stretching protocol (SP, n = 28). Participants in both groups will complete a digital daily exercise diary for the duration of the protocol.

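### The missing-value rule is attached to the 6-week analysis; the three-visit analysis of the aerobic programme is left as a mixed ANOVA that would conventionally use complete cases only

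*Protocol article*

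**What the plan says.** The Analysis section announces two separate analyses of the clinical outcomes.

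- **First analysis.** "Outcome measures will be analyzed using two-way mixed ANOVA at baseline and 6-week timepoints". The text then explains the interaction test and the simple-effect follow-up, and closes with "Should there be missing values, generalized estimating equation analysis will be employed". This analysis carries the primary outcome: "The primary clinical outcome is the RPQ at 6-weeks of intervention".
- **Second analysis.** "Outcome measures between groups (delayed-start vs. immediate start) following the aerobic exercise intervention only" are compared, and these "will be analyzed using two-way mixed ANOVA at the three primary timepoints: baseline, 6-weeks and 12-weeks". The item names its own method. It neither repeats the GEE sentence nor refers back to it.

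The Sample size section expects losses: "With an anticipated dropout rate of 1–5 participants per group we will recruit 56 participants for this trial". The Attrition and adherence section withdraws participants whose medication changes or who cannot attend follow-up, so some 12-week visits will be missing.

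**The concern.** A conventional two-way mixed ANOVA needs a complete row for each participant. Someone with baseline and week-6 scores but no 12-week score is left out altogether, including the data already collected. The plan attaches its only missing-value rule to the two-visit analysis, where fewer visits can be missed, and gives none for the three-visit analysis.

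The second analysis is the only stated clinical analysis that reaches 12 weeks, and the Abstract lists the RPQ at both 6 and 12 weeks as the primary outcome measure. If people who are not improving are likelier to stop, completers look better than the randomized group, and the benefit of the 12-week programme is overstated. Unequal loss between arms is also plausible. If the delayed arm does its 6 weeks of stretching and then the full 12-week programme, its last aerobic visit comes 6 + 12 = 18 weeks after the start, against 12 in the immediate arm.

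**Working it through.** **Inputs from the article.** 28 per arm (Treatment arms); 46 evaluable participants, alpha 0.05, 80% power, and 1 to 5 dropouts per group (Sample size); MCID 4.6 RPQ points (Primary outcome measure). The article gives no RPQ standard deviation, between-visit correlation or dropout mechanism, so these are assumed below and shown as ranges.

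**1. The plan's own figure.** 46 + 2 × 5 = 56. Equivalently, 46 / (1 − 5/28) = 46 × 28/23 = 56. The recruitment target reproduces.

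**2. Data at risk.** At the upper end, 5/28 = 17.9% per arm, or 10/56 = 17.9% overall. At the lower end, 1/28 = 3.6%. The upper figure assumes that all losses occur after week 6, so that baseline and week-6 scores exist to be discarded.

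**3. Precision.** For the change from baseline to week 6, complete cases use 23 per arm where 28 are observed. The standard error is multiplied by √(28/23) = 1.10, about 10% larger. The gain at 12 weeks is smaller, because those scores are truly missing.

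**4. Direction of bias.** Let D6 and D12 be the changes from baseline at 6 and 12 weeks, with common SD σ and common correlation ρ. Then Var(D6) = 2σ²(1 − ρ) and Cov(D12, D6) = σ²(1 − ρ), so the regression of D12 on D6 has slope 1/2. If leaving depends on a poor D6, completers overstate improvement at week 6, and at week 12 by half as much.

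**5. Size in RPQ points.** Simulation of one arm of 28, with a true change of −4.6 at both visits, SD 5.5 to 12 and ρ 0.5 to 0.7. *Moderate* means that the weight for leaving rises by a factor of 2.7 per SD of poorer week-6 change.

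| Missing week 12 (per arm) | Completers, week 6 | Completers, week 12 |
|---|---|---|
| 5, at random | about −4.6 | about −4.6 |
| 1, moderate | −4.8 to −5.0 | −4.7 to −4.9 |
| 5, moderate | −5.3 to −6.7 | −5.0 to −5.6 |
| 5, the worst responders | −5.9 to −8.2 | −5.3 to −6.4 |

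With five moderate losses, the 12-week overstatement is about 0.4 to 1.0 points, roughly half the week-6 figure of 0.7 to 2.0, as step 4 predicts. In SD units it is 0.4/5.5 = 0.07 to 1.0/12 = 0.08.

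**6. Size in SD units.** A second simulation used 28 per arm, correlations of 0.6 (adjacent visits) and 0.5 (baseline to week 12), and about 16% to 19% lost after week 6. The odds of loss rose 2.7 to 4.5 times per SD of worse week-6 change, and the true 12-week improvement was 0.80 SD. Completers showed 0.85 to 0.94 SD, an overstatement of 0.05 to 0.14 SD. A likelihood estimate from all observed visits gave about 0.80.

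**7. Between arms.** With identical true trajectories and identical loss, there was no false difference. With identical trajectories but 10% against 22% loss, completers showed a false week-6 difference of about 0.09 SD, and the all-data estimate showed none.

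**8. Would GEE be enough?** In the step-5 settings, GEE on all observed visits gave about −4.6 to −4.7. That owes something to the assumed structure: Cov(Y12, D6) = ρσ² − ρσ² = 0, so loss driven by D6 alone does not shift the observed 12-week mean. Unweighted GEE generally needs completely random loss.

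**The case against.** The strongest reply is that the GEE sentence is worded generally and stands immediately before the second analysis. The first item is where the method is explained, and the second reuses the named method. If the GEE rule is confined to the first item, so is the simple-effect rule, which is an unlikely intention. This reading is possible, and on it the gap closes. But the article calls the analyses separate and restates the method for the second, so the text does not settle the matter.

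It can also be said that missing-data handling for a secondary analysis belongs in the SAP or full protocol, which are not shown. That would hold if the article were silent. Here it states a rule and places it with one analysis, and for the other it names a method that conventionally drops incomplete rows.

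Some stronger inferences are tempting but not supported:

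- **That the plan deletes anyone who misses a visit.** No sentence says so. Deletion follows from how the method is usually run.
- **That the stretching-versus-aerobic contrast at week 6 is distorted.** The second analysis concerns the aerobic period only, and the natural reading aligns both arms on aerobic time. The treatment contrast belongs to the first analysis, where GEE is stated.
- **That the metabolite analysis has the same fault.** Its sentence can be read as a separate comparison at each visit, which drops nobody across visits.

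Finally, the larger figures take the top of the dropout range and assume that poor responders leave. The stated withdrawal reasons are medication change and inability to attend, not lack of improvement. The reduced number of completers is also allowed for in the recruitment target. These points limit the size of the problem but do not justify discarding observed week-6 scores.

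**Conclusion.** The point holds in a limited form. The missing-value fallback is stated with the baseline-to-6-week analysis and is not extended to the three-visit analysis, whose named method would conventionally be restricted to completers. The 17.9% figure rests on the plan's upper dropout and on all losses falling after week 6.

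The 12-week overstatement of 0.05 to 0.14 SD is conditional on loss being moderately to strongly related to poor week-6 response, and on the assumed correlations. With one dropout per arm and moderate dependence, it is about 0.1 to 0.4 points across the two visits. Under random loss there is no bias.

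The within-arm overstatement is the firmer result; bias between arms arises mainly if loss or response differs by arm. A reader might infer that the primary RPQ result is at risk, but the 6-week comparison has its own fallback and is untouched.

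**What to change.** In the second analysis, replace the mixed ANOVA with a likelihood-based linear mixed model fitted to all observed visits, with arm, visit and arm-by-visit terms and baseline retained as a visit. At minimum, state that the missing-value rule also covers this analysis. The mixed model is preferable because it remains valid when loss depends on earlier observed scores, provided the model is correctly specified. If the metabolite ANOVA is meant as a three-visit repeated-measures analysis, the same model can serve there.

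The cost is a change of wording while the trial is still recruiting; the model can be fitted in SPSS, the package that the Data management section implies. There is one small downside: with an unstructured covariance, the tests need not match those of the univariate ANOVA exactly, even with complete data.

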### Measures

The baseline assessment will include participant-reported instruments to collect information on demographics, past medical history, acute rest advice they received following mTBI and self-reported measures of physical and sedentary activity. Outcomes collected at baseline, following 6-weeks and 12-weeks of intervention include symptom burden, assessments of specific symptoms, exercise intolerance and MRI, including spectroscopy, detailed below. A blood draw will also be completed at these time points along with five nights of sleep actigraphy. An electronic follow up (E-FU) will be completed at 3 and 9-weeks post-AEP completion and include specific symptom questionnaires in addition to questions regarding exercise behavior since intervention completion.

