#### Brain imaging outcomes

Magnetic resonance brain imaging will be performed to investigate changes with the AEP and SP to better understand recovery or persistence of symptoms. The imaging protocol includes a T1-weighted structural acquisition, 1H magnetic resonance single voxel magnetic resonance spectroscopy (MRS), arterial spin labeling (ASL) to quantify tissue perfusion, and resting-state functional MRI. The MRS voxels will be in the sensorimotor cortex and the anterior cingulate. Of specific interest are the MRS biomarkers γ-aminobutyric acid (GABA) and glutathione that will be simultaneously measured using a new magnetic resonance spectroscopy method (HERMES, Hadamard Encoding and Reconstruction of MEGA-Edited Spectroscopy) [57]. Glutathione, an antioxidant that combats oxidative stress, is hypothesized to be reduced following brain injury and is expected to change with aerobic exercise. GABA is an inhibitory metabolite which is modulated with brain plasticity. It has been proposed that increased GABA impedes recovery from mTBI [58]. Additional metabolites of interest from MRS (that will be measured using a point-resolved spectroscopy, PRESS) are glutamate, a marker of excitability, and N-acetyl aspartate (NAA), a marker of neuronal health.

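### Regional perfusion tests are run only after a null whole-brain result, and the metabolite model is ambiguous and on neither reading the most precise test of week-6 change

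*Protocol article*

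**What the plan says.** All the relevant analysis sentences are in the protocol article's Analysis section.

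- **Metabolites.** "Metabolite levels will be compared using an ANOVA model comparing groups at each of the three timepoints (as above"). Earlier in the section, the second clinical analysis "will be analyzed using two-way mixed ANOVA at the three primary timepoints: baseline, 6-weeks and 12-weeks", and it concerns outcomes after the aerobic programme. The first clinical analysis uses baseline and week 6 only and is introduced with the remark that "Two-way mixed ANOVA allows for analysis of group by time interaction effect".
- **Perfusion (ASL).** The maps are processed and "group data will be compared on a whole brain basis". No timepoint is named. The next sentence is "If no differences are detected, regional analyses may be applied".
- **Resting-state fMRI.** "Resting state fMRI data will investigate differences in functional connectivity between groups and time points".

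Under Brain imaging outcomes, "The MRS voxels will be in the sensorimotor cortex and the anterior cingulate". The Measures section confirms that a baseline scan exists: "Outcomes collected at baseline, following 6-weeks and 12-weeks of intervention include symptom burden, assessments of specific symptoms, exercise intolerance and MRI, including spectroscopy". The third objective in the Background is about change in imaging biomarkers after each protocol. The Study design section makes the stretching group the control for the first 6 weeks only.

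**The concern.** **Perfusion.** The regional step is optional, is reached only when the whole-brain comparison is negative, and has no named regions. A null result can then be replaced by whichever region turns out positive, and a reader could not tell how many regions were examined.

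**Metabolites.** The objective is change, and the randomised aerobic-versus-stretching contrast exists at week 6 only. The sentence does not single out that contrast and does not make clear whether each person's baseline scan enters the model. Read literally, it tests groups visit by visit, including at baseline, where randomisation already makes the null hypothesis true. Read through its cross-reference, it points to a three-timepoint model written for a different question.

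At stake are a false-positive perfusion finding and a metabolite effect that is harder to detect than it need be. The Discussion relies on the metabolite data to explain response to the intervention.

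**Working it through.** The protocol gives no imaging sample size, effect size or error rate, so there is no stated figure to reproduce. The number of regions *k*, their correlation, and the baseline-to-follow-up correlation ρ are assumptions, shown over a range.

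**1. Perfusion, independent regions.** Whole-brain test at 0.05; if negative, *k* regional tests each at 0.05 uncorrected. Chance of at least one false positive = 0.05 + 0.95 × (1 − 0.95^k).
- k = 5: 0.05 + 0.95 × (1 − 0.774) = 0.265
- k = 10: 0.05 + 0.95 × (1 − 0.599) = 0.431

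**2. Perfusion, correlated regions.** Regions of one brain are not independent, so the null case was simulated: 28 per arm (the planned allocation), 40,000 runs, equally correlated regions, whole-brain value taken as their mean.

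| Correlation | k = 5 | k = 10 |
|---|---|---|
| 0.5 | 0.18 | 0.29 |
| 0.8 | 0.13 | 0.18 |

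The whole-brain test alone stayed near 0.05 throughout.

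**3. Would correction within regions be enough?** With each region at 0.05/k after a full 0.05 whole-brain test, under independence: 0.05 + 0.95 × (1 − (1 − 0.05/k)^k) = 0.097 at k = 5 and 0.096 at k = 10. This is much better, but still about twice nominal if both steps count as confirmatory.

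**4. Metabolites: two readings of the cross-reference.**
- *Separate comparisons at each visit.* The week-6 test uses the week-6 value only.
- *Two-way mixed ANOVA.* With baseline and week 6, the group-by-time test is a comparison of change scores. The only three-timepoint version in the section concerns outcomes after the aerobic programme, which is not the aerobic-versus-stretching contrast.

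**5. Precision at week 6.** With equal variances at the two visits, the variance of the group contrast relative to week 6 alone is 2(1 − ρ) for a change score and 1 − ρ² for ANCOVA (large-sample form).

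| ρ (assumed) | Week 6 only | Change or group-by-time | ANCOVA |
|---|---|---|---|
| 0.3 | 1 | 1.40 | 0.91 |
| 0.5 | 1 | 1.00 | 0.75 |
| 0.7 | 1 | 0.60 | 0.51 |

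Since 1 − ρ² = (1 − ρ)(1 + ρ) and 1 + ρ < 2, ANCOVA has smaller variance than both alternatives at every ρ strictly between 0 and 1. The change score beats week 6 alone only if ρ exceeds 0.5.

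**The case against.** A reader might infer that the imaging analyses as a whole ignore each person's baseline scan. A reader might also count 4 metabolites × 2 voxels × 3 timepoints = 24 tests, with a third of them spent on baseline. The documents do not support this. The cross-reference may well point to the mixed ANOVA, which is a within-person model and does use baseline. Resting-state fMRI is compared across time points, and the perfusion sentence names no timepoint at all. The test count holds only under the literal reading of one sentence. If the mixed ANOVA is meant, ANCOVA is a gain in precision rather than the correction of an error.

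On perfusion, 26% and 43% rest on independence, which is implausible within one brain, and every figure in steps 1 and 2 assumes no correction, which the article does not state. The list of regions, the correction across them and any multiplicity rule across metabolites may sit in an analysis plan that is not shown, so their absence from a condensed article is no fault in itself.

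These objections narrow the point but do not remove it. The null-result trigger is written into the article, and correction within regions alone would not bring the two-step error back to 5%. The metabolite sentence remains open to two readings, and neither gives the best available test of its own objective.

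**Conclusion.** The point holds in two limited parts.

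- **Perfusion: firm in kind, assumption-dependent in size.** The regional step is a second chance set off by a null result. With uncorrected tests, the chance of a false positive is about 13–29% for 5 to 10 regions correlated at 0.5–0.8, with 26–43% as the independence figures. Fewer regions or a correction would lower it.
- **Metabolites: ambiguous wording and avoidable loss of precision.** Against a week-6-only comparison, baseline adjustment removes 9%, 25% or 49% of the variance at ρ 0.3, 0.5 or 0.7. Against a change or group-by-time contrast it is also better at each value. The text does not establish that baseline is ignored.

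Nothing here touches the primary RPQ comparison at 6 weeks or the resting-state fMRI analysis. These are secondary, mechanistic outcomes, so the change is worth making but does not threaten the trial's main conclusion.

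**What to change.** **Perfusion.** Delete the condition that makes the regional step depend on a null whole-brain result. Name a short list of regions now; the two spectroscopy voxel locations are an obvious choice. Analyse them whatever the whole-brain result, correct across them, and label them exploratory. Dropping the condition does not by itself lower the chance of a false positive somewhere. The fixed list, the correction and the label do that work, while unconditional reporting stops a regional result from standing in for a null one. If a joint 5% error rate is wanted, split it in advance: 0.025 for the whole brain and 0.025/k per region gives about 0.049.

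**Metabolites.** Replace the ambiguous sentence with a named model: week-6 level by group, baseline level as covariate, as the leading contrast, with no significance test at baseline. Describe the 12-week data separately, since the stretching group is no longer a control by then. A multiplicity rule across metabolites and voxels can be left to the analysis plan.

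**Cost.** Wording only. No new scans or participants are needed, and recruitment was still under way when the article was submitted. The one downside is a stricter threshold for each individual region.
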